## Abstract

**Background:**

Dermatitis is a skin condition caused by multiple causes, including radiotherapy treatment. Pharmacological treatments can become chronic and are not exempt from side effects. The latest recommendations of the American Academy of Dermatology establish the use of natural, nourishing, and moisturizing cosmetic products as prevention and the first therapeutic step for dermatitis. Alantel® is a cream developed to reduce redness and irritation, promote the local immune system, combat immunosenescence, and promote the healing of epidermal lesions. The objective was to evaluate the effect of a cream (Alantel) based on natural products at high concentrations for the preventive and curative treatment (at early stages) of radiation-induced dermatitis in patients with breast cancer.

**Methods:**

Our protocol is an experimental, prospective, triple-blind, multicenter, controlled clinical trial with two parallel arms. The experimental group will be treated with Alantel, while the control group will receive another moisturizing cream. Radiotherapy oncology professionals will recruit a total of 88 patients (44 per comparison group) with breast cancer who will receive radiotherapy oncology treatment for 15 days, and they will be randomly allocated to the experimental or control group. Selected patients will be followed up for four visits by primary care physicians for up to 1 week after completion of radiotherapy. The main study variable will be the incidence rate of mild post-radiation dermatitis. An intention-to-treat analysis will be performed, applying a comparison test for independent means and proportions. A bivariate and multivariate analysis will also be developed to check the treatment effect, adjusting for predictive sociodemographic and clinical variables.

**Discussion:**

By carrying out this clinical trial, it is expected to verify that Alantel cream, based on natural products at high concentrations, has advantages over a moisturizing cream for the preventive and curative treatment of RD in patients with breast cancer. The COVID-19 pandemic has been influenced by delaying the start of the study. One of the main limitations of this study will be the time required to recruit the patients from the planned sample, given that the selection criteria are restrictive and, although the study is multicenter, recruitment will be coordinated through a single service on radiotherapy oncology.

**Trial registration:**

ClinicalTrials.gov NCT04116151. Registered on 4 October 2019.

## Introduction

### Background and rationale

Radiotherapy, the use of high-energy rays to either kill cancer cells or treat some benign tumors, is undoubtedly a positive intervention. However, as the primary mode of action in radiotherapy treatment is killing cells to prevent replication, other non-cancerous cells may be affected. For example, up to 85% of patients will experience some form of skin reaction, ranging from local erythema to moist desquamation. Such reactions are distressing and painful for the patient, and if severe enough, they may warrant treatment discontinuation [1].

According to the MSD manual [1], general treatment of dermatitis includes supportive care of cosmetic type (such as moisturizers, dressings, and antihistamines for itching), topical corticosteroids, and sometimes antibiotics or other drugs, or ultraviolet light therapy. Treatment of dermatitis depends on the cause and the specific symptoms. Depending on the severity of the process, this therapeutic ladder can be gradually climbed to treat the milder symptoms to the more severe and chronic ones.

According to the Society and College of Radiographers [2], topical emollients are commonly used to prevent radiation-induced dermatitis (RD) or to provide comfort for patients once a reaction has occurred. As radiation damages the basal cell layer of the skin, the normal desquamation of cells and growth of replacement cells are interrupted, and skin dehydration occurs. Topical emollients are used to hydrate the skin and ameliorate feelings of itching and soreness.

From this point on, all treatments are based on drugs and not cosmetics. However, the latter will serve on the following therapeutic steps to supplement hydration and soothe irritation and pruritus. Among these natural products are aloe vera and chamomile [3–5]. These agents, qualified as cosmetics, have been used to treat iatrogenic RD to alleviate the symptoms and signs of this condition [6–9]. Other studies report using other cosmetic therapies to relieve symptoms and signs of dermatitis [10, 11].

Cosmetics are the first level of treatment required for dermatitis [2]. In the case of RD, several studies report the prevention or treatment of RD with the application of skin products, including aloe vera gel [12], phospholipid-based anionic cream [13], wound healing ointment [14], corticosteroid therapy [15], or hyaluronic acid-based formulation [16]. In addition, washing the skin with soap and water during radiation therapy for cancer treatment may be helpful because it may eliminate various microorganisms that cause skin inflammation [17]. To date, however, no standard therapy or broad consensus on the optimal management of RD in cancer patients is available.

The Radiation Therapy Oncology Working Group has developed a scale of skin lesions after radiation therapy [18]. It comprises 5 degrees scored in ascending order based on severity. Acute or moderate injuries, which would be treatable with cosmetics, include categories 1 and 2: mild atrophy, mild hair loss, mild depigmentation, patch atrophy, and moderate telangiectasia.

However, we have found few clinical trials supporting or demonstrating the efficacy of these cosmetic products for treating RD. Therefore, we believe that providing scientific evidence about this is very appropriate and convenient.

Following these clinical protocols [1, 2] and the literature review on the effectiveness of cosmetics for hydration and relief of symptoms and signs of RD, we consider it relevant to investigate if a cream containing natural products is effective as a prophylactic procedure in breast cancer patients treated with radiation therapy. We focused on this type of cancer as it is one of the most frequent, and in which more patients could benefit if demonstrated that this product is useful. This could avoid climbing the therapeutic ladder toward treating RD with drugs that may lead to side effects. The current drugs cause a pharmaceutical expense that is mostly unproductive because these alone do not adequately manage nutrition, hydration, or de-epithelialization because they do not have the correct formulation. In addition, these treatments are not exempt from side effects, leading to symptoms continuing in the short to medium term.

## Objectives

A controlled clinical trial is planned to objectively evaluate the efficacy of a cosmetic cream. The purpose is to demonstrate that a topical preparation based on active ingredients of natural origin (Alantel®, based on aloe vera, chamomile, and thyme), with anti-inflammatory and epithelization properties, is effective (compared to a harmless product made up of a moisturizing substance), in prophylaxis or curative treatment of mild RD in radiation oncology used to treat breast cancer patients. We also want to assess the safety of this preparation.

As secondary objectives, we consider the following: (a) to check whether this preparation can reduce the discomfort caused by inflammation and cell death, which are the cause of the symptoms and morbidity of radiation-induced dermal lesions in radiation oncology; (b) to determine the health-related quality of life before and after treatment in women who are prescribed this cosmetic cream compared with women who do not use this cosmetic cream; (c) to demonstrate that the coordinated follow-up of this type of patients between Radiation Oncology and Primary Care improves its quality and the health care of these patients.

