**Interventions:**						
Alantel (Experimental group)		x	x	x	x	x
Placebo (Control group)		x	x	x	x	x

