#### Eligibility criteria

Inclusion criteria are as follows: patients aged 18 years or older diagnosed with breast cancer and who are going to start radiation therapy with a radical intention on the affected breast, by the hypofractionated scheme with integrated boost (40.05 Gy with integrated boost, 48 Gy, in 15 sessions), coming from centers involved in the project or that can be followed up by a participating primary care professional and that sign an informed consent.Exclusion criteria are as follows: patients with dermal lesions or invasive skin cancer or distant metastases; history of connective tissue disorders; severe mental disorder (dementia, drug addiction, etc.); history of hypersensitivity reaction to any of the ingredients in the study cream; history of severe/extensive burn, moisture, erosion, or drainage in the treatment area; or participants involved in other clinical trials within that month.

Fourteen collaborating clinical researchers (5 oncologists, 8 GP, and one primary care occupational therapist) will perform the therapeutic intervention to be tested.

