#### Interventions

Once the patient has been included in the study and allocated to one of the two groups, the radiation oncologists will collect demographics and existing pathologies and perform an initial assessment of the skin to be irradiated before the start of radiation therapy. The radiation oncologist will administer the patient a Quality-of-Life Assessment Questionnaire (Skindex-29) [19] and inform the family physician of the patient’s details, identification code, and probable date of initiation of radiation therapy so that the family physician can contact the patient prior to the start of the treatment to schedule follow-up visits.

At each follow-up visit after sessions 5, 10, and 15 and 1 week after completion of radiation therapy, the family physician will perform the following actions:

Evaluate patients’ irradiated skin according to the common toxicity criteria of the cooperative skin group suggested by the RTOG Foundation (https://www.rtog.org) [18].Likewise, patients presenting with dermatitis will be asked to assess and quantify the discomfort and pain related to dermatitis symptoms and signs on an analog ordinal scale (from 1 to 10).Complete the Skindex-29 Quality of Life Questionnaire [19] (https://www.bibliopro.org/buscador/294/cuestionario-dermatologico-de-calidad-de-vida-skindex-29).Record adverse events (AE): Possible AE will be evaluated and reported during the study, and their causal relationship with the components of the cream will be assessed. If an adverse reaction is found, the researcher will evaluate the intensity and frequency of each episode and decide whether or not additional treatments are needed. These side effects will be notified to the Andalusian Pharmacovigilance Center through the yellow card alert system. If the physician considers it appropriate, the patient will be withdrawn from the study.

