## Discussion

By carrying out this clinical trial, it is expected to verify that Alantel cream, based on natural products at high concentrations, has advantages over a moisturizing cream for the preventive and curative treatment of RD in patients with breast cancer. One of the main limitations of this study will be the time required to recruit the patients from the planned sample because the selection criteria are restrictive, and although the study is multicenter, recruitment will be coordinated through a single service of radiotherapy oncology. The COVID-19 pandemic caused the study to be delayed and could not start at the scheduled time. In addition, this influenced the patient recruitment process because accessibility to the health system was restricted and the research staff suffered an increase in the demand for care, focusing their efforts on the care of cancer patients with COVID-19.

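### The protocol claims curative as well as preventive efficacy, but contains no randomised comparison of cure in established radiation dermatitis

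*Protocol article*

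**What the plan says.** **The claim.** The Objectives section sets out to show efficacy "in prophylaxis or curative treatment of mild RD in radiation oncology used to treat breast cancer patients". The abstract's Background gives the aim as evaluating the cream "for the preventive and curative treatment (at early stages) of radiation-induced dermatitis in patients with breast cancer". The abstract's Discussion and the main Discussion both expect to find that Alantel "has advantages over a moisturizing cream for the preventive and curative treatment of RD in patients with breast cancer". The Background and rationale is narrower: it asks only whether such a cream is "effective as a prophylactic procedure in breast cancer patients treated with radiation therapy".

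**The design.** Eligibility criteria admit patients "who are going to start radiation therapy with a radical intention on the affected breast" and exclude "patients with dermal lesions or invasive skin cancer or distant metastases". Under Interventions, the oncologist will, after allocation, "perform an initial assessment of the skin to be irradiated before the start of radiation therapy". Table 1 marks both creams at allocation (t = 0) and at every visit from t1 to t4. No day of first application is given in the text.

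**Where cure is made operational.** The Outcomes text names RD incidence as the primary outcome. Table 2 lists a second item under its primary heading: a three-level grading of lesion course, from no better to fully cured. Statistical methods then plans Cox regression with RD, improvement and cure as dependent variables, to judge the product's effect after adjustment. The Sample size section uses RD incidence alone (46.7% vs 78.6%).

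**The concern.** A claim of curative efficacy needs a comparison, protected by randomisation, of what happens to established RD with and without the product. Here the only randomisation precedes radiotherapy, and no passage describes randomising patients, or starting cream, once RD is present. Any comparison of healing among RD cases is therefore between patients who developed RD on Alantel and patients who developed it on the control cream. If Alantel prevents RD as the sample size assumes, these are differently selected groups and a difference in healing has no clear cause.

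What is at stake is the conclusion. The protocol already words its expected finding as preventive and curative. A positive incidence result, perhaps with a favourable cure model beside it, would fit that wording although the curative part has no randomised support. The bias can also run against the product and hide a real benefit.

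**Working it through.** **1. What the sample size covers.** Inputs from Sample size: p1 = 0.467 (Alantel), p2 = 0.786 (control), alpha 0.05 (taken as two-sided), power 80%, loss 20%, ratio 1:1. With the pooled-variance formula and no continuity correction:

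n = [1.960 × √(2 p̄(1 − p̄)) + 0.842 × √(p1(1 − p1) + p2(1 − p2))]² / (p2 − p1)²

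where p̄ = (0.467 + 0.786)/2 = 0.6265.

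- Numerator: (1.960 × 0.684 + 0.842 × 0.646)² ≈ 3.55
- Denominator: 0.319² = 0.1018
- n ≈ 34.9, so 35 per group
- 35/(1 − 0.20) = 43.75, so 44 per group and 88 in total

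The stated figure is reproduced. It is a calculation for RD incidence only.

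**2. Who could enter a cure comparison.** Expected RD cases = patients per group × assumed RD rate.

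| Patients per group | Alantel | Control | Total |
|---|---|---|---|
| 35 (after 20% loss) | 35 × 0.467 = 16.3 | 35 × 0.786 = 27.5 | 43.9 |
| 44 (no loss) | 44 × 0.467 = 20.5 | 44 × 0.786 = 34.6 | 55.1 |

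**3. What selection alone can do.** The protocol gives no cure rates, so those below are assumptions for illustration. Suppose the cream has no curative effect and prevents only the milder cases. Of every 100 control patients, 46.7 would get severe-prone RD and 31.9 (78.6 − 46.7) mild-prone RD. On Alantel only the 46.7 severe-prone cases remain.

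- Cure 20% in severe-prone and 60% in mild-prone RD: Alantel 20%; control (0.467 × 0.20 + 0.319 × 0.60)/0.786 = 0.285/0.786 = 36%.
- Cure 30% and 50%: Alantel 30%; control (0.467 × 0.30 + 0.319 × 0.50)/0.786 = 0.300/0.786 = 38%.

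The cream looks worse at curing RD without having any effect on cure. The direction depends on which cases are prevented. If the 31.9 prevented cases were the severe-prone ones and the 46.7 remaining were mild-prone, the 20% and 60% rates would give Alantel 60% and control (0.467 × 0.60 + 0.319 × 0.20)/0.786 = 0.344/0.786 = 44%. That is an apparent curative benefit that does not exist.

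**4. Power, setting selection aside.** This uses a two-sided two-proportion test at 0.05 with the group sizes from step 2 and assumed control cure rates of 30% to 50%.

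| Gain in cure | 35 per group | 44 per group |
|---|---|---|
| 20 points | 24–26% | 30–32% |
| 31.9 points (same size as the incidence effect) | 55–56% | 65–67% |

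The planned Cox models are not identical to this test, so these figures are indicative.

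**The case against.** The strongest reply is that the protocol does evaluate cure. Both creams continue to t4, so patients who develop RD keep using their assigned product. Table 2 records improvement and cure, and also onset and duration. RD presence, toxicity, symptoms and evolution time are collected at every visit from t1 to t4, and models for cure are planned. All of this stands. A reader might infer that the design can say nothing except about prevention, or that cure is never examined; the documents do not support that. Examining cure does not make the comparison randomised, however, and the planned analysis is the one affected by selection.

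Two further inferences should also be resisted. One is that healing can be seen only at the visit a week after radiotherapy. Lesion course is recorded at all four visits, and no passage says that skin cannot improve during treatment. The other is that joining prophylaxis and cure with an or in the Objectives lets the trial succeed on either half. The Outcomes text names RD incidence alone as primary and the sample size follows it; the looser point is Table 2, which adds lesion course under the same heading.

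It is also fair that toxicity grade, Skindex-29 and freedom from RD at t4 can be compared across all randomised patients. Those comparisons are valid, but they measure a strategy of cream started early and continued, not cure of existing RD.

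**Conclusion.** The point holds in this form: the protocol claims curative efficacy without a randomised comparison of cure in established RD. The improvement and cure analyses it plans cannot supply one, because they condition on an event after randomisation that the cream is expected to change from 78.6% to 46.7%. They would rest on about 16 against 28 patients (21 against 35 with no loss) and have no sample-size basis. In the assumed scenarios, selection alone shifts the cure comparison by 8 to 16 points.

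The case counts depend on the protocol's own RD rates. The sizes of bias and power depend on cure rates that the documents do not give. That cream starts before radiotherapy is read from the marks in Table 1, since the text gives no day of first use. The incidence question is untouched, and N = 88 is correct for it.

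**What to change.** - **Objectives, abstract (Background and Discussion) and main Discussion:** limit the confirmatory objective and the stated conclusion to prevention of RD by cream started before radiotherapy and continued. This also brings them into line with the Background and rationale.
- **Table 2:** take lesion improvement or cure out of the primary outcomes, in line with the Outcomes text. Without this step a prevention-only objective would contradict the table.
- **Statistical methods:** label the improvement and cure analyses among RD cases as exploratory and state that they do not support a curative claim. Alternatively, define the outcome in all randomised patients, for example RD-free at t4, and interpret it as the effect of the whole strategy.
- **Timing:** Trial status says the study concluded in June 2023. The change therefore applies to the analysis and the report, and should be disclosed there as made after completion.

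No new patients or data are needed. The cost is a narrower product claim.

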## Trial design

The Alantel study is designed as a randomized, controlled, multicenter, superiority, triple-blind trial, with two parallel groups.

### Methods: participants, interventions, and outcomes

#### Study setting

A total of 88 breast cancer patients undergoing radiation therapy will be recruited into the radiation oncology clinic and allocated to the experimental group (EG: Alantel) or the control group (CG: moisturizing cream), with an allocation ratio of 1:1 (see flowchart; Fig. 1). Both groups will receive a 15-session (3 weeks) hypofractionated radiation therapy, subject to the usual hygienic recommendations.

**Fig. 1 Fig1:**
[figure not shown]
Flowchart of the research phases of the Alantel study

Table 1 shows the schedule of the main events of the study, both the recruitment process and the intervention, and follow-up and evaluation visits.

**Table 1 Tab1:** Schedule of enrolment, interventions, and assessments from the Alantel study

Time point	Enrolment	Allocation	Study period			Close-out
			Post-Allocation			
	*t* = 0	*t* = 0	*t*1 = 5 days Start RT	*t*2 = 10 days Start RT	*t*3 = 15 days Start RT	*t*4 = 22 days After RT
**Enrolment:**						
Eligibility screen	x					
Informed consent	x					
Allocation		x				
**Interventions:**						
Alantel (Experimental group)		x	x	x	x	x
Placebo (Control group)		x	x	x	x	x
**Assessments**						
**List baseline variables**		x				
Assigned group		x				
Sociodemographic data		x				
Previous history of dermatitis		x				
**List outcome variables**						
Presence/absence of radiodermatitis (RD)			x	x	x	x
Toxicity Level (ORTG Criteria)			x	x	x	x
Degree of discomfort with RD			x	x	x	x
Quality of life related to health			x			x
Presence of adverse events			x	x	x	x

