**Secondary outcomes**	
Onset and duration of RD	Time of onset and duration of post-radiation dermatitis
Toxicity in patients’ irradiated skin	Common toxicity criteria of the cooperative group for skin suggested by the RTOG Foundation (https://www.rtog.org) [18]
Discomfort and pain concerning symptoms and signs related to dermatitis	Degree of skin discomfort caused by radiation. Subjective assessment and quantification by the patient on an ordinal scale (0 to 10) Pruritus, pain, itching, or peeling of the skin
Quality of life	Quality of life of patients with skin conditions Skindex-29 questionnaire [19]

In addition, secondary outcomes include the level of toxicity in patients’ irradiated skin. It will be assessed according to the common toxicity criteria of the cooperative group for skin suggested by the RTOG Foundation (https://www.rtog.org) [18] according to which toxicity is classified into five levels: 0 for no toxicity or no change; 1 for scattered macular or papular rash or erythema that is asymptomatic; 2 for scattered macular or papular rash or erythema with pruritus or other associated symptoms; 3 for symptomatic generalized macular, papular, or vesicular rash; and 4 for exfoliative dermatitis or ulcerative dermatitis.

The assessment of discomfort and pain concerning symptoms and signs related to dermatitis is based on the subjective assessment and quantification by the patient on an ordinal scale (range 0 to 10), the Visual Analogic Scale (VAS), answering the following question: What score would you rate from 0 (where 0 is the situation where you do not feel symptoms such as pruritus, pain, itching, or peeling of the skin) to 10 (where 10 is the situation where you notice the most symptoms) to your skin problem where do you have the lesion?

Quality of life will be assessed by completing the Skindex-29 questionnaire. Skindex-29 is a self-administered questionnaire to measure the quality of life of patients with skin conditions every 4 weeks, consisting of 29 items. The Spanish version of Skindex-29 has been validated [19].

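### Table 1 shows no pre-treatment Skindex-29 although the text plans one, so the baseline for objective (b) must be fixed

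*Protocol article*

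**What the plan says.** Objective (b) in the Objectives section is "to determine the health-related quality of life before and after treatment in women" using the cream, compared with women who do not use it. The Statistical methods section plans a pre-post comparison of the endpoints, using the results of each visit.

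Two places set the timing of the questionnaire:

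- **Table 1.** The row "Quality of life related to health" has marks at t1 and t4 only. Both t=0 columns (enrolment and allocation) are empty. The rows for the two creams are marked from allocation onward.
- **Interventions.** Once the patient is included and allocated, "The radiation oncologist will administer the patient a Quality-of-Life Assessment Questionnaire (Skindex-29"), at a point when the family physician has yet to contact her ahead of treatment. The same section then lists the Skindex-29 among the actions at every follow-up visit: after sessions 5, 10 and 15, and one week after radiotherapy ends.

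The last visit is labelled "22 days After RT" in Table 1, against one week after the end of radiotherapy in Interventions and Recruitment.

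**The concern.** A before-and-after comparison needs a value taken before radiotherapy and before the randomised cream. Table 1 is the schedule of assessments, so a site could reasonably work from it, and its earliest Skindex-29 comes when both have started.

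A t1 score is measured after randomisation and may already carry part of the treatment effect. As the starting point of a change score it subtracts that part. As an adjustment covariate it can adjust part of the effect away. A team that reads the first recorded questionnaire as the baseline would therefore be estimating something other than objective (b).

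**Working it through.** **1. The plan's own figure.** The only design figure is the sample size for dermatitis incidence, in the Sample size section: 46.7% against 78.6%, alpha 0.05 (taken as two-sided), power 0.80, 20% loss.

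n per arm = [1.960·√(2·0.6265·0.3735) + 0.842·√(0.467·0.533 + 0.786·0.214)]² / 0.319² ≈ 34.9, so 35.

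35/0.80 = 43.75, so 44 per arm and 88 in total. This reproduces the stated figure. No quality-of-life quantity enters it, so the present point leaves it untouched.

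**2. Is the t1 mark an artefact of the table layout?** No. Read into the same six columns, the row "Sociodemographic data" falls under allocation t=0, the eligibility screen under enrolment t=0, and presence of dermatitis under t1 to t4. The columns line up. The table can show a baseline assessment and does not do so for quality of life.

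**3. The two schedules side by side.**

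| Time point | Table 1 | Interventions text |
|---|---|---|
| t=0, before radiotherapy | no | yes |
| t1, session 5 | yes | yes |
| t2, session 10 | no | yes |
| t3, session 15 | no | yes |
| t4, close-out | yes | yes |

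They disagree at t=0, t2 and t3: three of five.

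**4. What change from t1 estimates.** Let d1 and d4 be the true differences between arms in mean score at t1 and t4. Randomisation makes the expected difference at t=0 zero.

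- Change from t=0 estimates d4 − 0 = d4.
- Change from t1 estimates d4 − d1.
- If d1 = f·d4, change from t1 shows (1 − f)·d4.

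The document gives no value for f, so the size of the loss cannot be stated. It is zero only if nothing has separated the arms by t1.

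**5. What a true baseline adds.** With correlation r between the t=0 and final scores, ANCOVA multiplies the variance of the unadjusted final-score comparison by about 1 − r². The document gives no r. Over an assumed range of 0.5 to 0.7 the factor is 1 − 0.25 = 0.75 to 1 − 0.49 = 0.51.

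**6. The t4 label.** Counting by session, 15 + 7 = 22, which agrees with one week after the end. Counting calendar days (15 weekday sessions from a Monday), sessions 5, 10 and 15 fall on days 5, 12 and 19, and one week later is 19 + 7 = 26. On either scale used consistently the gap is 7 days. Only the literal label, 22 days after radiotherapy, contradicts the text.

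**The case against.** The strongest reply is that a baseline is planned. Interventions puts a Skindex-29 before radiotherapy, objective (b) agrees with it, and nothing says that Table 1 overrides the text. Statistical methods does not specify a change from t1 either. A randomised comparison of final scores needs no baseline to be unbiased. All of this stands, and it makes the harm conditional. It does not remove the contradiction, because two explicit schedules cannot both describe what was done.

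A reader might infer more than the document supports:

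- **That the trial has no baseline.** This follows only if Table 1 was the schedule used.
- **That there is a third schedule.** The Outcomes section says the questionnaire is there to "measure the quality of life of patients with skin conditions every 4 weeks". That sentence describes the instrument and sets no trial visits. It states no recall period, so it cannot show that the on-treatment readings overlap.
- **That a sample-size penalty can be stated.** If 25% to 50% of the effect were present at t1, 1/0.75² = 1.78 and 1/0.5² = 4 would suggest 1.8 to 4 times the patients. The early share is assumed, and so are equal variances of the two change scores. With correlations of 0.5 (t=0 to t4) and 0.7 (t1 to t4), change variances of 2(1 − r) are 1.0 and 0.6 in units of the score variance. The multipliers then become 0.6·1.78 = 1.07 and 0.6·4 = 2.4. The figure is too dependent on its assumptions to use.
- **That the last visit falls 3 days after radiotherapy.** The subtraction 22 − 19 takes a session count from one scale and a calendar day from the other.
- **That the on-treatment questionnaires should go.** Removing them is a trade-off and is not needed to resolve the contradiction.

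**Conclusion.** The contradiction is certain: Table 1 omits the pre-treatment Skindex-29, and the t2 and t3 ones, that the text requires. The consequence is conditional. If Table 1 was followed, objective (b) and the pre-post analysis lack a true baseline, and change from t1 understates the final difference by whatever share had appeared by then. That share cannot be quantified from the document. If the text was followed, the baseline exists and only the table is wrong. Either way, t1 must not serve as the baseline.

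This should be corrected, but it does not threaten the trial's main conclusion. Quality of life is a secondary outcome, and the 88 patients rest on dermatitis incidence. The precision gain in step 5 of the working rests on an assumed correlation.

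**What to change.** Trial status says the study concluded in June 2023, so the collected data cannot change. The analysis and the report still can.

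1. State which schedule the sites followed. Correct Table 1 to show the Skindex-29 at t=0, before radiotherapy and first cream use, and reconcile the t1 to t3 marks with Interventions.
2. Name the t=0 form as the baseline for objective (b). Check from recorded dates that it was completed before the cream was first used, since the text places it after allocation.
3. Compare the final (t4) score between arms by ANCOVA, with arm and t=0 score as terms. Do not use t1 as a baseline or covariate.
4. If t=0 forms were not collected, compare final scores between arms without change from t1, and report that the pre-treatment value for objective (b) is unavailable.
5. Reword the t4 label to agree with the text, and label t1 to t3 by session number.

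The cost is a table correction, one or two sentences on the analysis and a check of existing forms. No new data are needed.
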